## Conclusion

The DUET study is a randomized controlled trial that will provide evidence whether US-accelerated thrombolysis will significantly reduce therapy time compared with standard thrombolysis in patients with recently thrombosed infrainguinal native arteries or bypass grafts, without an increase in the number of complications.

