**Discussion:**

The DUET study is a randomized controlled trial that will provide evidence of whether US-accelerated thrombolysis will significantly reduce therapy time in patients with recently thrombosed infrainguinal native arteries or bypass grafts, without an increase in complications.

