## Background

Thrombosis of an infrainguinal bypass graft or the native lower leg arteries has been associated with a high rate of limb loss and significant morbidity and mortality [1]. Traditional therapy with thrombectomy and eventually additional (bypass) surgery has been associated with moderate long-term patency rates [2]. Catheter-directed thrombolysis was introduced in the early 1980s as a treatment option for occluded bypass grafts. This technique has advantages that make it ideal for acute occlusions, including avoidance of mechanical injury to the endothelium, no need for surgical interventions and more complete lysis of the clot in the bypass graft or outflow arteries. Moreover, it can dissolve platelet-fibrin aggregates in the microcirculation and thrombi in collateral vessels [3].

A recent systematic review that included a meta-analysis of 5 large randomized controlled trials with a total of 1283 patients comparing surgery with thrombolysis in the management of acute lower limb ischemia showed no significant difference between them in limb salvage or death at 30 days, 6 months, or 1 year. However, hemorrhagic complications and distal embolization were more likely at 30 days in thrombolysis patients (8.8% and 12.4%, respectively) than in surgery patients [4,5].

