## Methods/Design

### Study objectives

The purpose of the study is to demonstrate that US-accelerated thrombolysis will significantly reduce (by at least 12 hours) therapy time compared with standard thrombolysis, without increasing complication rate.

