#### Sample size calculation

The assumption has been made that the mean duration for successful standard thrombolytic treatment of infrainguinal native arteries or bypass grafts is 2.5 ± 1 day, based on retrospective series from the St. Antonius Hospital, Nieuwegein. Given a power of 90% and a 2-tailed significance of 5%, a 2-armed randomized trial including 26 patients in each arm will be needed to prove a significant reduction in therapy time (12 hours or more) with US-accelerated thrombolysis compared with standard thrombolysis. Taking into account 5% to 10% dropouts in each arm, 30 patients need to be included in each study arm. We will analyze the primary outcome by means of Kaplan-Meier and Log-rank test. The sample size calculation is also based on this premise. We will assess imbalance in prognostic factors as a secondary analysis by means of Cox-proportional Hazards multivariate analysis.

An interim analysis on the primary end point (ie, efficacy) will be performed after 50% of patients have completed their follow-up. The Peto approach will be followed, meaning that the study will only be stopped for beneficial effects in case of a *P *< .001 [15]. The study will not be stopped in case of futility. End points in blinded groups will be assessed by the DSMB.

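### The objective is to demonstrate shorter lysis without more complications, but 30 patients per arm cannot demonstrate the second half

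*Protocol article*

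**What the plan says.** The Study objectives section gives the purpose as demonstrating a reduction of at least 12 hours in "therapy time compared with standard thrombolysis, without increasing complication rate". Three other places carry the same idea less firmly. The Hypothesis states it as something the investigators anticipate. The Discussion paragraph of the abstract ("without an increase in complications") and the Conclusion ("without an increase in the number of complications") say that the trial will supply evidence on the question.

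The Sample size calculation section concerns therapy time only. It assumes a standard-arm mean that "is 2.5 ± 1 day, based on retrospective series" from one hospital, and 26 patients per arm "to prove a significant reduction in therapy time (12 hours or more") with 90% power at a two-sided 5% level, raised to 30 per arm for dropouts. The log-rank test and the interim analysis named there are also on the primary endpoint.

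Hemorrhagic, distal thromboembolic and other complications are listed separately under Secondary endpoints. Hemorrhagic complications are defined under Definitions. The article gives no expected complication rate for this trial and no margin for an acceptable increase. The Background reports, from a meta-analysis of surgery versus thrombolysis, that "hemorrhagic complications and distal embolization were more likely at 30 days in thrombolysis patients (8.8% and 12.4%, respectively").

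**The concern.** Demonstrating that a rate does not rise means excluding, with stated confidence, a rise large enough to matter. A trial sized for a difference in a time endpoint gives no assurance of that for events affecting roughly one patient in ten. The stated purpose has two parts, and the design figures support only one of them.

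This matters because the article presents shorter lysis as a way to reduce bleeding and other complications, and says there has been no earlier randomized trial of ultrasound-accelerated lysis in this setting. An objective worded as a demonstration of no increase invites a claim at the end of the trial that the data could not carry, even if the two arms had identical counts.

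**Working it through.** **The plan's own figure.** The stated 26 per arm is for therapy time. With a difference of 0.5 day, SD 1 day, two-sided 5% and 90% power, the two-means formula 2(1.96 + 1.28)²(1/0.5)² gives about 84.1, so 85 per arm. The stated 26 is not reproduced. That is a separate matter, and nothing below depends on it. The dropout step is in order: 26/(1 − 0.10) = 28.9, so 29, against 30 stated.

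**Inputs.** n = 30 per arm (Sample size calculation). Hemorrhage 8.8% and distal embolization 12.4% (Background). These two are literature figures for thrombolysis, used here as assumptions; a range of 5% to 20% is shown as well.

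**Expected events per arm.** 30 × 0.088 = 2.6 hemorrhages; 30 × 0.124 = 3.7 embolizations.

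**Precision with identical observed counts (Newcombe 95% interval).** With Wilson limits l and u for each arm and equal proportions p, the half-width is √[(p − l)² + (u − p)²].
- 3/30 in each arm: l = 0.035, u = 0.256, half-width √(0.065² + 0.156²) = 0.169, so −16.9 to +16.9 points.
- 4/30 in each arm: l = 0.053, u = 0.297, half-width √(0.080² + 0.163²) = 0.182, so −18.2 to +18.2 points.
- 0/30 in each arm: the upper limit is still +11.4 points.

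**Sensitivity to the assumed rate.** The large-sample half-width is 1.96√[2p(1 − p)/30].

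| Assumed rate, both arms | Half-width (points) |
|---|---|
| 5% | 11.0 |
| 8.8% | 14.3 |
| 12.4% | 16.7 |
| 20% | 20.2 |

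At 8.8%, equal observed rates would leave a true ultrasound-arm rate of about 8.8 + 14.3 = 23% unexcluded, which is 2.6 times the assumed rate.

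**Power to detect a doubling, 30 per arm, two-sided 5%.** Fisher power sums the binomial probabilities of all tables with P ≤ 0.05. The normal approximation is Φ{[|p₂ − p₁| − 1.96√(2p̄(1 − p̄)/n)] / √[(p₁(1 − p₁) + p₂(1 − p₂))/n]}, with p̄ the mean of p₁ and p₂. For 8.8% to 17.6% this is Φ[(0.088 − 1.96 × 0.0874)/0.0867] = Φ(−0.96) = 0.17.

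| Event | Rates | Fisher | Normal approximation |
|---|---|---|---|
| Hemorrhage | 8.8% to 17.6% | 7% | 17% |
| Distal embolization | 12.4% to 24.8% | 14% | 23% |
| Sum, no overlap assumed | 21.2% to 42.4% | 32% | 42% |

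**What showing no increase would take.** The article names no margin, so these are illustrations. With equal true rates, one-sided 2.5% and 80% power, n per arm = (1.96 + 0.84)² × 2p(1 − p)/m². A 10-point margin m needs 126 per arm at 8.8% and 171 at 12.4%. Even a 15-point margin needs 56 and 76. All exceed 30.

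**The case against.** Several points on the other side are sound and limit what can be said.

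- Only the Study objectives section speaks of demonstrating. The Hypothesis states an expectation, and the abstract and Conclusion pose a question on which evidence will be gathered. A reader might infer that all four places promise a no-harm result; the wording does not support that for three of them.
- A reader might infer that no analysis of complications is planned. The document does not establish this. It is a journal article, and methods for secondary endpoints are commonly left to the full protocol or the SAP, neither of which is shown.
- A reader might also infer that a non-significant result will be taken as proof of safety. No section says so. It is a risk created by the wording, not a stated rule.
- The 8.8% and 12.4% are background figures for two separate complication types, while the objective speaks of a single complication rate. A combined rate would yield more events and more power. The Background also cites a small series of ultrasound-accelerated lysis without complications.
- Secondary endpoints need not be powered. Most trials sized on efficacy are imprecise for safety, and this one has a safety board and adverse event reporting.

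None of this rescues the objective. The summed rate raises Fisher power for a doubling only to about 32%. Zero events in both arms would still leave +11.4 points. Monitoring protects participants but does not demonstrate equality of rates. The point concerns an objective and a sample size that both stand in this document, so it does not depend on what an unseen SAP contains.

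**Conclusion.** The objective is wrong as written. With 30 patients per arm the trial can estimate complication rates but cannot demonstrate that they do not increase. Identical counts at the expected event numbers leave about ±17 to ±18 points, and assumed rates from 5% to 20% give about ±11 to ±20 points. A doubling of either complication alone would be missed in most trials of this size, and so would a doubling of the two rates summed without overlap.

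The conclusion rests on the stated 30 per arm and on the literature rates as assumptions; it is not sensitive to the rate within the range shown. It does not call into question the choice of primary endpoint, and it does not ask for complications to be powered.

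**What to change.** Reword the Study objectives so that demonstration applies to therapy time only and complications are estimated as secondary endpoints. Specify the between-arm risk difference with its 95% confidence interval for hemorrhagic complications, as defined under Definitions, and for distal thromboembolic complications. Add that a non-significant difference will not be reported as showing no increase. Bring the Hypothesis, the Discussion paragraph of the abstract and the Conclusion into line with this.

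No extra patients or procedures are needed. The cost is a few sentences and a less favourable stated claim.
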